## Sensitivity analyses

We will perform sensitivity analyses using a full analysis set (FAS) and a per protocol set (PPS). The FAS analysis will exclude participants who never ingest the ONS in the ONS group and those who are later found not to meet the eligibility criteria from the population for the ITT analysis. The population for the PPS analysis will comprise participants who ingested an average of ≥ 200 ml of the ONS per day.

We will also perform sensitivity analyses using a generalized linear mixed model with repeated measures analysis to estimate the mean difference in the change of the percentage of BWL.

### Methods in analysis to handle protocol non-adherence and any statistical methods to handle missing data {20c} {20c-p}

All analyses will be on an intention-to-treat (ITT) basis. Randomized patients will be included and will be analyzed according to their allocated group regardless of what postoperative management they received. We will exclude the patients who have no available data and with protocol violations, such as patients who are later found not to meet the eligibility criteria.

We will document the amount of and reasons for missing data, if possible, between the ONS and control group. In case of dropout, we will describe the timing of dropout and, if possible, the reason.

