### Criteria for discontinuing or modifying allocated interventions {11b}{18b(ii)-p}

The assessments, including HRQoL questionnaires, will be continued unless the participants withdraw consent for assessments. The following criteria will be used to discontinue the intervention:The participant requests discontinuation of the explanatory treatment.The participant cannot continue the explanatory treatment due to adverse events.The patient is found to be ineligible after initiation of treatment.The patient stops coming to the hospital due to relocation, etc.The patient dies.The study investigator determines that it is not appropriate to continue the explanatory treatment for any other reasons.

Unless the participant wishes to have his/her data destroyed or excluded, his/her already collected data will be retained and analyzed.

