### Plans to promote participant retention and complete follow-up {18b} {18b(ii)-p}

The attending physician plans the patients’ clinic appointments according to the time points of the outpatient clinic when the study participant will be assessed (at T2, T3, and T4). The data center will send an email reminder to each investigator before the time point of the outpatient clinic. If participants miss a scheduled follow-up appointment, the primary physician will try to call them to visit to the outpatient clinic. For patients who drop out from this study, data will be included as intention-to-treat.

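### The primary population is called ITT but excludes randomised patients for open-ended protocol violations and later-found ineligibility, which contradicts the article's own FAS definition

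*Protocol article*

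**What the plan says.** Three statements in the protocol article decide who enters the primary comparison.

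- Section {20c}, on non-adherence and missing data, opens with the principle: "All analyses will be on an intention-to-treat (ITT) basis". It adds that randomised patients "will be analyzed according to their allocated group regardless of what postoperative management they received".  The abstract makes the same ITT promise.
- The same paragraph then continues: "We will exclude the patients who have no available data and with protocol violations". Later-found ineligibility is given there as an example of a violation; the list is not closed.
- The section on sensitivity analyses builds the FAS by removing two groups: ONS-arm patients who never took the product, and "those who are later found not to meet the eligibility criteria from the population for the ITT analysis". The PPS is then defined by average ONS intake.

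Two other places bear on the question. The retention section ({18b}) says: "For patients who drop out from this study, data will be included as intention-to-treat". The section on discontinuing the intervention ({11b}) lists ineligibility found after treatment has begun as a reason to stop. It says that, unless the participant asks otherwise, "his/her already collected data will be retained and analyzed".

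The blinding section ({17a}) states that patients, physicians and statisticians all know the allocation.

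**The concern.** An ITT comparison is protected because membership of each group is fixed at randomisation. A rule that removes patients afterwards for violations or ineligibility gives up that protection unless the grounds were fixed before allocation and are judged without knowledge of the arm. The article states neither condition, and the people who would apply the rule know the arm.

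The open-ended wording leaves the choice of what counts as a violation until after the data are in. Eligibility is not wholly mechanical either: Table 1 lets investigators exclude patients they judge otherwise unsuitable. Some criteria may also come to light unevenly. Allergy to the study product is an exclusion criterion, and an unrecognised allergy is most likely to show itself in the arm that takes the product.

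At stake is the headline result. Two analysts working from this text could build different primary sets, and both would report theirs as ITT.

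**Working it through.** **Step 1. Set the two rules side by side.** Let R be all randomised patients, E those later found ineligible, V those with any other protocol violation, M those with no available data, and N the ONS-arm patients who never took the product.

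- Principle in {20c}: ITT = R, as allocated.
- Exclusion sentence in {20c}: ITT = R minus M, E and V, with V undefined.
- Sensitivity analyses: FAS = ITT minus N and E.

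Under the exclusion sentence, E has already gone, so removing E to form the FAS does nothing. The FAS definition makes sense only if E is still in the ITT set. The two sections therefore give different primary populations.

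**Step 2. Locate non-ingesters.** N leaves only at the FAS step, and low intake matters only at the PPS step. The principle in {20c} keeps patients whatever management they received. Non-ingesters therefore stay in the ITT set.

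**Step 3. Check the planned sample size.** Inputs from *Sample size {14}*: difference 3 points, SD 5.5, two-sided alpha 0.05, power 80%, 1:1.

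- n per arm = 2 × (1.96 + 0.842)² × 5.5² / 3² = 52.8, rounded up to 53, so 106 in total. This matches the stated figure.
- 106 / 0.90 = 117.8, so 118, consistent with about 120.
- Normal-approximation power is 84.8% with 60 per arm, 80.9% with 54 and 80.2% with 53.

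The size is sound, and keeping all randomised patients does not raise it.

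**Step 4. Illustrate the bias, on assumed figures.** The documents give no exclusion count and no outcome for excluded patients. If k of n patients lie on average d points above their arm's mean %BWL and are removed, the mean of those remaining falls by k × d / (n − k). With n = 60:

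| k removed, one arm | d = 6 | d = 8 |
|---|---|---|
| 3 | 3×6/57 = 0.32 | 3×8/57 = 0.42 |
| 6 | 6×6/54 = 0.67 | 6×8/54 = 0.89 |

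Against the 3-point target these are about 11%, 14%, 22% and 30%.

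**Step 5. Effect on the false-positive rate, same assumptions.** Take no true effect, SD 5.5, removal from the ONS arm only, d = 5.5 (one SD), and SE = 5.5 × √(1/60 + 1/(60 − k)).

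- k = 3: shift 0.29, SE 1.02, two-sided error about 5.9%.
- k = 6: shift 0.61, SE 1.03, two-sided error about 9.1%.

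**Step 6. Exclusions in both arms.** If the same k and d apply to each arm, the shifts cancel and the net effect on the difference is 0. With 6 removed in one arm and 3 in the other, the net shift is 0.67 − 0.32 = 0.35 (d = 6) or 0.89 − 0.42 = 0.47 (d = 8).

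**The case against.** The best defence is that the article names only one violation, ineligibility. Eligibility is screened twice, the second time at the enrolment where allocation is made, and most criteria concern facts settled by then. Removal on such facts, applied equally in both arms, need not bias the comparison. That is right as far as it goes. It does not help the undefined violations, and the article does not say that the safeguard applies.

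A reader might also infer several stronger things that the documents do not support.

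- *That patients who do not take the ONS are dropped from the primary analysis as one-arm violators.* Step 2 shows the opposite.
- *That the retention and discontinuation sections declare ineligible patients to be ITT.* The retention sentence concerns dropouts only. The discontinuation section says collected data are analysed but names no analysis set. The firm contradiction is between {20c} and the FAS definition.
- *That everyone with any missing value is excluded.* The text says no available data, which is narrower. A t test on 8-week %BWL cannot use a patient without an 8-week weight unless a value is filled in, and an article may leave imputation to the fuller plan.
- *That uneven detection is established.* The one-month outpatient check concerns the ONS diary, not eligibility. Uneven detection is plausible, not shown.
- *That the 11 to 30% shift estimates the bias.* It is a one-arm worst case on assumed counts and gaps.

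**Conclusion.** The point stands in this form. The article states its primary-population rule in two ways that cannot both hold. Followed literally, the exclusion sentence produces a set that is not ITT and is open to selection after randomisation, in a trial where the statisticians also know the arm. This is more than detail left to an analysis plan, because the article does state the rule and states it inconsistently.

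The size of any bias is unknown. The range of 0.32 to 0.89 points rests on three assumptions: 3 to 6 exclusions, all in one arm, each group averaging 6 to 8 points above that arm's mean. Balanced exclusions would remove most of it. The case for correction rests on the contradiction and the open wording, not on these figures.

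**What to change.** In {20c}, delete the exclusion for protocol violations and later-found ineligibility. State instead that the primary analysis includes every randomised patient, in the allocated group, who has the outcome data the analysis needs, and that nobody is removed for a protocol violation or for ineligibility found later.

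Confine those removals to the FAS and PPS sensitivity analyses. Say there that eligibility is judged on facts that existed before randomisation and in the same way in both arms.

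Report by arm how many patients lack an 8-week weight. Keep the repeated-measures model already planned as a sensitivity analysis, since it can also use patients who have later weights. Making that model or imputation primary is a separate choice that this correction does not require.

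The cost is one paragraph of wording, with no new data and no change to the sample size. The article reports that recruitment ended on 5 January 2024, so the wording should be settled before the primary analysis is run.

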### Plans to give access to the full protocol, participant‑level data, and statistical code {31c}

Full protocol, participant-level data, or statistical code details will not be published. Unpublished data will be made available upon reasonable request.

## Oversight and monitoring

### Composition of the coordinating center and trial steering committee {5d}

Kyoto University will serve as the coordinating center. Only the investigators and members of the data center will have access to the anonymized data in EDC. The coordinating center and the data center will meet online to review the progress of the trial once a month. The content confirmed in the meetings will be shared with investigators at other institutions during the monthly online study meetings and via email.

### Monitoring {21a}

The data will be monitored by another researcher (SH) at Kyoto university, who is not involved in the data collecting, and the data managers at the data center every 6 months.

In the EDC system, all data entries will be checked in real-time, allowing for immediate identification of missing data or common errors. The paper booklets will be also checked upon arrival at the data center, and if there are any discrepancies, inquiries will be made. KU, YT, and the data center will monitor data collection via the EDC and paper booklets. If data collection is delayed, reminders will be sent to each researcher via email.

### Adverse event reporting and harms {22}

Adverse events are defined as any unfavorable and unintended symptom, disease, or any sign of such (including an abnormal laboratory finding) in the research subjects. The Ministry of Health, Labor, and Welfare of Japan publication, “Ethical Guidelines for Clinical Studies: Questions and Answers,” defines severe adverse events (SAEs) as follows: (i) Results in death; (ii) Is life-threatening; (iii) Requires inpatient hospitalization or prolongation of existing hospitalization; (iv) Results in persistent or significant disability or incapacity; or (v) Is a congenital anomaly defect in offspring.

The investigators will promptly report SAEs to the chief investigator at each hospital. Then, the chief investigator will report SAEs to the director of the hospital and principal investigator. The SAEs are shared with all investigators by the principal investigator. Data about all SAEs will also be collected in the EDC.

### Frequency and plans for auditing trial conduct {23}

No formal audits will be performed because this study’s intervention can be classified as a “minimally invasive intervention.”

### Protocol amendments {25}

Any amendments of the protocol will be submitted to the Institutional Review Boards (IRB) of the Kyoto University Graduate School of Medicine for approval by primary investigator. Then, a copy of the amended protocol will be sent to the other investigators and the amended protocol will also be submitted to the IRBs of the other participating institutions. We will report to the participants as necessary.

If there are any deviations from the protocol, they will be documented using a breach report form and notify the other participating institutions after consideration of severity at the IRB of the Kyoto University Graduate School of Medicine.

### Dissemination plans {31a}

The results of this study will be published in a peer-reviewed journal and presented at national and international medical congresses.

## Patient and public involvement

Neither patients nor the public were involved in the design, conduct, reporting or dissemination plans of this research.

## Discussion

One of the important outcomes for patients with gastric cancer after gastrectomy is BWL. Previous studies investigating ONS for patients after gastrectomy have reported inconsistent results for this outcome [14–17, 28, 43]. This study will evaluate the effects of ONS with carbohydrate and protein on BWL, muscle strength, and HRQoL in the comparison with usual care. If this study shows better outcomes in the ONS group, it will provide evidence supporting the enhancement of postoperative daily activity in patients, better adherence to adjuvant chemotherapy, and better long-term prognosis.

Postoperative muscle strength and HRQoL after gastrectomy will be also examined. This simple ONS has 10 g of whey protein, including branched-chain amino acids, per 200 ml, which might help to prevent decreases in muscle strength. This potential beneficial outcome has been underappreciated [48], and this study will add novel evidence that might support this benefit.

Moreover, few studies have gathered information on energy intake from the regular diet [17]. We will collect the data on various nutrients in the regular diet, including on carbohydrates, protein, and fat, to assess the influence of ONS on the intake of energy and protein from the regular diet.

In previous studies, the common problem with ONS for patients with gastric cancer after surgery is poor adherence to ONS, which is reported to be approximately 45% to 68% of planned intake volume [14, 16, 43]. These studies [14–17, 28, 43] have used various types of ONS, and there is a possibility that these well-balanced oligomeric formulas or elemental diets could compromise the texture of ONS and lead to decreased adherence. If the adherence to ONS is higher than historical data [14, 16, 43] and some kinds of efficacy are shown compared with usual diet, patients with gastric cancer after gastrectomy can be offered practical alternatives with more acceptable texture.

To summarize, we have reported the protocol for a multicenter, open-label, parallel RCT that aims to evaluate the efficacy of ONS with simple nutritional ingredients for BWL following gastrectomy for gastric cancer. It is anticipated that the study findings will enhance our understanding of the benefits of ONS following gastrectomy and provide valuable insights into patient adherence and the effects on physical fitness and HRQoL. These insights could potentially transform postoperative care practices for patients with gastric cancer.

## Trial status

The protocol version number is jRCTs051230012 and the date of registration is 13 April, 2023. Patient recruitment began in 13 April 2023 and has finished at 5 January 2024.

## Data Availability

The final dataset will be accessible by the investigators of Kyoto University. The disclosure of contractual agreements between the funder and Kyoto University investigators do not limit the access to the final dataset for the investigators.

## Abbreviations

ONS: Oral nutritional supplements
KEGG: Kyoto Esophageal and Gastric Cancer Surgery Group
BWL: Body weight loss
HRQoL: Health-related quality of life
DG: Distal gastrectomy
